**Modified clinical success:**

- Complete modified clinical success

Complete modified clinical success will be declared when both (a) and (b) have occurred:

(a) Normalisation of SBP, defined as  $SBP < 135 \text{ mmHg}$  on home BP; if home BP not available, then defined as  $SBP < 140 \text{ mmHg}$  on clinic BP

(b) Not taking any antihypertensive medications

- Partial modified clinical success

Partial modified clinical success will be declared when the criteria for complete success are not met, and either (a) or (b) has occurred:

(a) reduction in SBP, with no increase in antihypertensive medication, i.e. both of (i) and (ii) have occurred:

(i) SBP has reduced by  $\geq 20 \text{ mmHg}$ , or has normalised, since baseline (based on home BP if available, otherwise based on clinic BP)

(ii) the number of classes of antihypertensive medication being used is no more than 1 more than at baseline

(b) reduction in antihypertensive medication, with no increase in SBP, i.e.

(i) SBP is unchanged since baseline (based on home BP if available, otherwise based on clinic BP); unchanged SBP defined as a change in either direction of  $< 20 \text{ mmHg}$

(ii) the number of classes of antihypertensive medication being used has reduced by 2 or more since baseline, or the use of antihypertensive medication has been stopped

- Absent modified clinical success

An absence of modified clinical success will be declared when neither partial nor complete modified clinical success can be declared.

## **1.10. STATISTICAL ANALYSIS PLAN (SAP)**

### **1.10.1. SAP OBJECTIVES**

The objective of this SAP is to describe the statistical analyses to be carried out for the MATCH Study.

**1.10.2. GENERAL PRINCIPLES**

Continuous data will be summarised as the number of observations and number of missing values, mean, standard deviation, median, quartiles, and range. Categorical data will be summarised as the number of observations and number of missing values, frequencies, and percentages.

Continuous measures collected at baseline and follow-up will be summarised at each time point separately, and as changes from baseline. Missing follow-up values may be carried forward from earlier visits for selected analyses; in such instances, summary data will be presented both without, and with imputation.

Groups will be compared using appropriate independent samples tests, with results presented as estimated between-group difference (or other comparative statistic), with 95% confidence interval, and p-value. Regression-based methods will also be used, adjusting for baseline values where appropriate, and for other baseline characteristics. Details of adjustment variables will be reported as part of the statistical outputs.

**1.10.3. CURRENT PROTOCOL**

The current study protocol at the time of writing is version 6.0, dated 25/11/2020. Following discussions with the Chief Investigator, and with input from the Trial Steering Committee, the analyses outlined in this SAP differ from those in the protocol; it is planned that the protocol will be amended to reflect these changes.

**1.10.4. DEVIATIONS TO THOSE SPECIFIED IN STUDY PROTOCOL**

This SAP does not cover the analyses of data relating to 18F-CETO PET CT. A separate plan will be developed for this part of the study.

The primary outcomes specified in this SAP relate to the PASO criteria for biochemical and clinical cure. These are similar to, but more scientifically relevant than the primary outcomes specified in the current protocol.

**1.10.5. ADDITIONAL ANALYSES TO THOSE SPECIFIED IN STUDY PROTOCOL**

No major additional analyses to those outlined in the protocol are planned.

**1.10.6. SOFTWARE**

Data will be analysed using R Version 3.6.2 or later. The final report will be provided as a Word document.

## **2. ANALYSIS POPULATIONS**

The “Enrolled Population” (EP) will consist of those who gave consent and met all inclusion/exclusion criteria.

The “Full Analysis Set” (FAS) will consist of those members of the EP who underwent both diagnostic tests (AVS and PET CT).

The “Substudy Population” (SP) will consist of those members of the EP who had one PET scan on spironolactone and one PET scan off spironolactone.

The numbers in each population will be reported. Reasons for exclusion from the FAS will be summarised. For those in the FAS, the numbers of participants who were randomised to each scan order, and who received the scans in each order, will be reported.

### **2.1. SUBJECT DISPOSITION**

For those in the FAS, the number and percentage of participants who completed each study visit will be reported.

### **2.2. BASELINE CHARACTERISTICS**

#### **2.2.1. PARTICIPANT CHARACTERISTICS AT SCREENING**

The following information collected at screening will be summarised for all participants in the Enrolled Population, in the Full Analysis Set, and in the Substudy Population; for those in the FAS, data will be presented according to whether the participant later underwent surgical treatment:

- Age, sex
- Height, weight, BMI
- Ethnicity
- Smoking history, alcohol consumption
- Medications
  - Number of different classes of antihypertensive medications being used, and whether using each class of medication
  - Total defined daily doses of antihypertensive medications being used, and defined daily doses of each class of medication
- Medical history
  - coded by MedDRA system organ class
- Physical examination
  - Presence of cardiovascular, respiratory, abdominal, neurological, genitourinary, musculoskeletal, and other abnormalities
- Clinic readings of systolic blood pressure, diastolic blood pressure, heart rate (mean of last two measurements to be used)
- ECG
  - presence of atrial fibrillation, and U-wave abnormalities

- Blood biomarkers
  - Sodium, potassium, creatinine, eGFR, urea, bicarbonate, troponin (hs-TnT), brain natriuretic peptide, renin mass, renin activity, aldosterone, aldosterone renin ratio (ARR) calculated with renin activity ( $ARR_{\text{activity}}$ ) and with renin mass ( $ARR_{\text{mass}}$ )

### 2.2.2. AVS RESULTS

For the FAS, whether ACTH was administered will be summarised, as will reasons for not administering ACTH. Serum ACTH will be summarised as a whole and in relation to whether ACTH was administered.

For the FAS, the following AVS measures will be summarised as a whole, and in relation to whether the results indicated bilateral adrenal hyperplasia (BAH), unilateral aldosterone-producing adenoma (APA) (left), unilateral APA (right), or were inconclusive:

- Right Adrenal Vein
  - a. Cortisol (maximum value recorded per patient)
  - b. Aldosterone (value corresponding to maximum cortisol)
  - c. Aldosterone/Cortisol Ratio (b/a)
- Left Adrenal Vein
  - a. Cortisol (maximum value recorded per patient)
  - b. Aldosterone (value corresponding to maximum cortisol)
  - c. Aldosterone/Cortisol Ratio (b/a)
- Lateralisation Index (ratio of higher to lower A/C ratio)
- Low IVC
  - a. Cortisol (mean value recorded per patient)
  - b. Aldosterone (mean value recorded per patient)
  - c. Aldosterone/Cortisol Ratio (maximum value recorded per patient)
- Selectivity Index (Right) – ratio of A/C ratios between right adrenal vein and low IVC
- Selectivity Index (Left) – ratio of A/C ratios between left adrenal vein and low IVC

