Aside from the obvious advantages of being non-invasive and, potentially, affording greater capacity for investigating PHA (only a handful of interventional radiologists in the UK are able to perform AVS to a good standard), there are several reasons why we consider C-metomidate PET-CT is likely to be superior in distinguishing unilateral from bilateral disease. First, international consensus criteria on the interpretation of AVS demand stringent thresholds to reliably establish whether excessive aldosterone production lateralises to one side or the other. (17) Aldosterone (A) and cortisol (C) values are measured in both adrenal veins and in the lower part of the inferior vena cava (IVC), and a 'normalised' aldosterone value (A/C ratio) calculated for each side. Evidence of lateralisation (i.e. 'dominance' of aldosterone production by one adrenal gland) is considered to be present if (i) the A/C ratio on one side is  $\geq 4$  times that on the other side **and** (ii) the A/C ratio in the 'non-dominant' (or 'suppressed') vein is less than that in the IVC. BAH is diagnosed if the A/C values in each adrenal vein differ by  $\leq 2$ -fold, which leaves an equivocal ('grey') area (A/C ratio of 2-4) in which clinical decision-making is controversial. (26)

As already indicated, given that many physicians are inherently reluctant to pursue PHA investigations to their conclusion, clinical caution dictates that a substantial proportion of patients with ambiguous or non-diagnostic results from initial AVS do not progress to further investigation or surgery. Second, it is an important requirement for AVS that patients

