### **2.3.2. SECONDARY OUTCOMES**

Secondary (and Primary) outcomes will be compared between participants who underwent surgery and those who did not, and for those who underwent surgery, between those for whom surgery was indicated by AVS only, 11C-Metomidate PET-CT only, or both tests.

Linear, binary logistic, or ordinal logistic regression models will be used, as appropriate. Models will be adjusted for age and sex, and the baseline measure of the outcome (where appropriate). To assess differences between those who underwent surgery and those who did not, a categorical variable for whether surgery was performed will be included. To assess differences between AVS and 11C-Metomidate PET-CT, a 3-level categorical variable for whether surgery

was guided by AVS only, 11C-Metomidate PET-CT only, or both tests, will be included.

Similar models will be used to investigate other predictors of outcome after surgery, in the subset of participants who underwent surgery. In line with the secondary objectives, there is particular interest in the following predictors:

- BP response to therapy with spironolactone/eplerenone, measured as:
  - achievement of home SBP <135 mmHg (or clinic SBP <140 mmHg) at week 4
  - achievement of home SBP <135 mmHg (or clinic SBP <140 mmHg) at week 4, without an increase in other BP medication (as per PASO criteria)
  - change in SBP (home SBP if available, or clinic SBP) between baseline and week 4
  - change in SBP (home SBP if available, or clinic SBP) between baseline and week 4, correcting for changes in other BP medication
- Age, sex, ethnicity
- Baseline BP
- Number of classes of antihypertensive medication at baseline
- Tumour genotype, individually and grouping KCNJ5 mutations vs all other mutations
- Tumour immunohistochemical classification
- AVS parameters
  - Contralateral suppression (aldosterone/cortisol in the contralateral adrenal vein < 50% of aldosterone/cortisol ratio in IVC)
  - Contralateral suppression (aldosterone/cortisol in the contralateral adrenal vein < 100% of aldosterone/cortisol ratio in IVC)
- PET parameters
  - number of nodules on each side
  - 'Probability of adrenal adenoma' on contralateral side'
  - SUVmax (TOF) for [hottest] tumour/normal on side of tumour
  - SUVmax (TOF) for [hottest] tumour/liver
  - SUVmax ratio (tumour /contralateral adrenal) using SharpIR;
- 24h-urine steroid profile

Univariate, and multivariable models will be fitted to explore these associations.

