### **2.3.6. SENSITIVITY ANALYSES**

The primary analyses will be repeated after the exclusion of subjects for whom AVS was a technical failure.

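### The SAP's AVS Selectivity Index is a ratio of A/C ratios, so it does not measure the cortisol step-up and reads below 1 in a well-sampled suppressed gland; its IVC denominator is also a maximum where the component hormones are means

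*Combined protocol and SAP*

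**What the plan says.** SAP 2.2.2 lists the AVS measures to be summarised. For each adrenal vein these are the highest cortisol, the aldosterone from that same sample, and their ratio (A/C). For the low IVC, cortisol and aldosterone are per-patient means, but the third item is "Aldosterone/Cortisol Ratio (maximum value recorded per patient".

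The Selectivity Index is then the "ratio of A/C ratios between right adrenal vein and low IVC" for the right side and the "ratio of A/C ratios between left adrenal vein and low IVC" for the left.

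SAP 2.3.2 names two AVS predictors of outcome after surgery, both called contralateral suppression: "aldosterone/cortisol in the contralateral adrenal vein < 50% of aldosterone/cortisol ratio in IVC" and "aldosterone/cortisol in the contralateral adrenal vein < 100% of aldosterone/cortisol ratio in IVC". It does not say which IVC value is meant.

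Protocol 4.2, describing international consensus criteria, requires for lateralisation a fourfold A/C difference and also that "the A/C ratio in the 'non-dominant' (or 'suppressed') vein is less than that in the IVC". Protocol 11.0, the trial's working rule, asks only for the fourfold difference. It says that ACTH stimulation helps to confirm cannulation, but gives no numerical criterion.

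SAP 2.3.6 contains the one planned sensitivity analysis: "The primary analyses will be repeated after the exclusion of subjects for whom AVS was a technical failure". Technical failure has no numerical definition.

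**The concern.** A selectivity index would be expected to show whether the catheter was in the adrenal vein. The documents never say this in so many words, but the name implies it. Protocol 11.0 ties confirmation of cannulation to ACTH stimulation, and SAP 2.2.2 picks the adrenal sample by its cortisol. Both point to a cortisol gradient between adrenal vein and IVC.

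The SAP instead uses a quotient that describes relative aldosterone output, and later uses the same quotient under another name. A reader of the selectivity table would take low values as poor sampling, when on the suppressed side of a lateralising patient low values are what good sampling should give.

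The choice of the maximum IVC ratio is a second problem. It pushes the quotient in one direction and could carry over into a secondary predictor.

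**Working it through.** The plan states no figure on this point, so there is nothing to reproduce. The check is algebra, followed by an illustration.

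**1. What the index measures.** Let A and C be aldosterone and cortisol.

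- SAP index = (A_vein / C_vein) / (A_IVC / C_IVC).
- Let s be the cortisol step-up, so C_vein = s × C_IVC.
- Let r be the relative A/C, so A_vein / C_vein = r × (A_IVC / C_IVC).
- Then SAP index = r. The step-up s drops out.

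For step-ups of 5, 10, 20 and 40 combined with r = 0.2, 0.5 and 0.9, the index is 0.2, 0.5 and 0.9 throughout.

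**2. Overlap with suppression.** Contralateral suppression in SAP 2.3.2 is (A/C contralateral vein) / (A/C IVC), cut at 0.5 and at 1.0. On the contralateral side this is the formula in step 1. If both use the same IVC value, a Selectivity Index below 1 there and suppression at the 100% cut are the same event. On the dominant side the formula is not a suppression measure, so the overlap is one-sided.

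**3. Direction of the reading.** The second criterion in protocol 4.2 puts r below 1 in the suppressed vein. A catheter that draws IVC blood has r of about 1.

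Illustration with assumed values that are not in the documents: IVC A = 1000 and C = 700, so IVC A/C = 1.43; adrenal-vein C = 14000 when cannulated.

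| Sample | A | C | SAP index | Cortisol ratio |
|---|---|---|---|---|
| Dominant, cannulated | 60000 | 14000 | 4.29 / 1.43 = 3.0 | 20 |
| Bilateral disease, cannulated | 30000 | 14000 | 2.14 / 1.43 = 1.5 | 20 |
| Suppressed, cannulated | 7000 | 14000 | 0.50 / 1.43 = 0.35 | 20 |
| Missed, IVC blood | 1000 | 700 | 1.43 / 1.43 = 1.0 | 1 |

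The dominant and suppressed veins give a lateralisation ratio of 4.29 / 0.50 = 8.6, which meets the fourfold rule. The SAP index nevertheless ranks the correctly sampled suppressed vein below the miss. The cortisol ratio separates cannulated from missed in every row.

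**4. The IVC denominator.** Mean A / mean C is a cortisol-weighted average of the individual A/C ratios, so the maximum ratio can never be below it. It exceeds it whenever there are several samples with differing ratios.

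Assumed three-sample example: A = 900, 1000, 1100 and C = 750, 700, 650.

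- Individual ratios: 1.20, 1.43, 1.69; maximum = 1.69.
- Mean A / mean C = 1000 / 700 = 1.43.
- Quotient with the maximum, relative to the quotient with the means: 1.43 / 1.69 = 0.844, about 16% lower.
- Equivalent cut-offs on the means-based scale: 1.69 / 1.43 = 1.18, so the 100% cut acts as about 118% and the 50% cut as about 59%.

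The direction is certain. The size depends on how much the IVC samples vary, which the documents do not give.

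**The case against.** The best defence is that the index does nothing. It is one of several AVS measures to be summarised among the baseline characteristics, has no threshold, and is not cited in any population, model or exclusion. The AVS classification by which it is summarised (bilateral, left, right, inconclusive) is not described as derived from it. Protocol 11.0 relies on a common AVS protocol, audited centres and MDT assessment; protocol 24.3 adds an independent endpoints committee that reviews AVS. The cortisol gradient can be worked out from values already listed. The documents nowhere define selectivity as a cortisol ratio. And a reading far from 1 does at least suggest blood unlike the IVC sample.

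Most of this stands, and it limits the consequences. It does not rescue the definition. If an A/C quotient was intended, the label is wrong; if sampling quality was intended, the formula is wrong. Low and high readings cannot be ranked as worse and better placement.

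The objection to the denominator point is that SAP 2.3.2 does not say which IVC A/C it uses. That is correct, so the bias in the predictor is conditional. But SAP 2.2.2 gives the only definition of that quantity, and an analyst would naturally take it.

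**Conclusion.** The point holds as a defect of definition that should be corrected before analysis. The algebra needs no assumption. The reading below 1 rests on the suppression criterion in protocol 4.2. Cortisol as the intended basis is an inference from the name, from protocol 11.0 and from the SAP's own sample selection. The over-calling of suppression needs several differing IVC samples and use of the maximum in SAP 2.3.2, and it touches a secondary predictor only.

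A reader might go further and infer that the sensitivity analysis in SAP 2.3.6 would drop the wrong patients. The documents do not support that. Nothing says technical failure is judged by this index, and the planning table in SAP 1.5 treats unilateral and unsuccessful AVS as separate results.

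Nor do the AVS-unilateral rows measure harm. They hold 35 of the 56 percentage points operated (62.5%, about 44 of 70 patients), but not all need show suppression, because protocol 11.0 requires only the fourfold ratio.

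What the table does show is that classifying failures matters in general. Under the scoring rule in SAP 2.3.1, the expected PET-CT minus AVS accuracy is (19.5 − 5.5)/56 = 25.0 points. With the 11 points of operated AVS failures removed, it is (9.5 − 4.5)/45 = 11.1 points. That is a reason to keep an unsuitable index out of the rule, not evidence that it is in it. An effect on the primary comparison or its sensitivity analysis is possible but not shown.

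**What to change.** Change these lines in the SAP:

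- **2.2.2, Selectivity Index:** on each side, adrenal-vein cortisol divided by low-IVC cortisol, both already listed there.
- **2.2.2, existing quotient:** keep it if wanted, but relabel it as a relative A/C (suppression) ratio.
- **2.2.2, IVC A/C:** mean aldosterone divided by mean cortisol, consistent with the two items above it.
- **2.3.2:** state that contralateral suppression uses that same IVC value.
- **2.3.6:** state how AVS technical failure is determined, and that the A/C quotient is not used for it.

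The cost is a few lines of text. All values are already collected, and the population, endpoints and primary analysis are unchanged.

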## **11.0 Diagnostic Investigations**

The primary control intervention is AVS and will be performed according to an identical protocol

at all centres whose internal audit data indicate a successful bilateral cannulation rate of >75%. Briefly, the femoral vein is cannulated under local anaesthesia and catheters advanced under fluoroscopic guidance into each adrenal vein.(17) The procedure is performed under conditions of ACTH stimulation, which facilitates unequivocal confirmation of secure adrenal vein cannulation. Blood samples from both adrenal veins and the lower part of the inferior vena cava are analysed for aldosterone (A) and cortisol (C) and an aldosterone/cortisol (A/C) ratio calculated at each site. Lateralisation (providing evidence for an adrenalectomy to be recommended) is deemed to exist if the A/C value in one adrenal vein is at least 4-fold higher than the other. In preparation for AVS, treatment to control blood pressure is limited to a non-dihydropyridine calcium antagonist (e.g. verapamil) and doxazosin (together with potassium supplementation as needed), as the treatments least likely to interfere with interpretation of aldosterone/renin measurements. Although some rise in blood pressure is permitted in preparation for AVS, severely hypertensive patients may require additional therapy according to clinical judgement.

The experimental intervention is  $^{11}\text{C}$ -metomidate PET-CT. There has been no change in the protocol used since the proof-of-concept study. Patients are treated with dexamethasone 0.5 mg 6-hourly for 3 days, then receive an injection of 250 mBq (on average) of  $^{11}\text{C}$ -metomidate, with CT and PET scanning of the adrenal area 20-30 minutes later. A positive (lateralization) result is indicated by a maximum standardised uptake at least 25% greater in one adrenal gland compared to the other.

The assessment of the two diagnostic modalities will be undertaken at a monthly MDT of endocrinologists and radiologists. Patients will be offered surgery if one or both techniques indicate unilateral disease. For the very small number of cases (we estimate 1 in 25 on the basis of the proof-of-concept study), where AVS and  $^{11}\text{C}$ -metomidate PET-CT each meet these criteria for lateralisation, but to opposite sides, we will defer to the Trial Steering Committee (TSC) (see section 11).

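### The SAP builds the AVS Selectivity Index from A/C ratios, so it measures aldosterone suppression and cannot tell a selective sample from a missed vein

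*Combined protocol and SAP*

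**What the plan says.** SAP 2.2.2 lists the AVS measures to be summarised in the Full Analysis Set. The Selectivity Index is the "ratio of A/C ratios between right adrenal vein and low IVC" and, on the other side, the "ratio of A/C ratios between left adrenal vein and low IVC". For the low IVC, cortisol and aldosterone are taken as means, but the ratio is "Aldosterone/Cortisol Ratio (maximum value recorded per patient"). For each adrenal vein the list also holds "Cortisol (maximum value recorded per patient"), with the matching aldosterone.

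Three other places bear on how the index should be read:

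- Protocol 4.2 describes the consensus criteria for lateralisation. Besides a four-fold difference between sides, they require that A/C in the non-dominant "vein is less than that in the IVC".
- SAP 2.3.2 names contralateral suppression as a predictor of surgical outcome. One version is "aldosterone/cortisol in the contralateral adrenal vein < 50% of aldosterone/cortisol ratio in IVC"; the other uses 100%.
- Protocol 11.0 says that AVS is done under ACTH stimulation, "which facilitates unequivocal confirmation of secure adrenal vein cannulation". It names no measure and no cut-off.

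SAP 2.3.6 states: "The primary analyses will be repeated after the exclusion of subjects for whom AVS was a technical failure". Neither document defines technical failure.

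**The concern.** A selectivity index should show whether the catheter was in the adrenal vein. The documents point to the response to ACTH as what makes that clear, and the AVS list in SAP 2.2.2 holds two vein measurements, cortisol and aldosterone. Aldosterone is the quantity under test, which leaves cortisol relative to the IVC. An index that divides by cortisol in both numerator and denominator discards that information.

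The SAP also gives one ratio two names with opposite readings. On the non-dominant side a low value is a good sign in 2.3.2 (the gland is suppressed) and a bad sign in 2.2.2 (poor selectivity).

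At stake is the evidence that AVS was done well. Protocol section 23 rests the clinical value of the comparison on best-practice AVS, at centres with a bilateral cannulation rate of at least 75%. A reader of the results will look to the Selectivity Index to confirm this and will find low values in clearly lateralising studies. A further risk is that whoever writes the technical-failure rule for 2.3.6 takes up the only measure in the SAP that bears the name selectivity.

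**Working it through.** The plan gives no figure for this index, so there is none to reproduce. The check is algebraic.

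**Inputs.** From the documents: the definition (SAP 2.2.2), a suppressed gland's A/C below that of the IVC (Protocol 4.2), and the cell percentages in Protocol section 33. Assumed, because the documents give no values: cortisol step-up k of 5 to 40 fold when selective; a missed vein yields IVC-like blood, with 0 to 10% adrenal blood mixed in; the maximum IVC A/C exceeds a typical draw by d = 5% to 20%.

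**1. What the index measures.** Let A and C be aldosterone and cortisol, subscript v the adrenal vein and i the IVC. Write C_v = k·C_i and let s be the vein's A/C relative to the IVC's, so A_v = s·k·A_i.

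- SAP index = (A_v/C_v)/(A_i/C_i) = (s·k·A_i)/(k·C_i) ÷ (A_i/C_i) = s.
- Cortisol ratio = C_v/C_i = k.

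The step-up k drops out. On the non-dominant side, s below 0.50 or 1.00 is the contralateral-suppression criterion of SAP 2.3.2.

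**2. Values under each condition.**

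| Sample | SAP index | Cortisol ratio |
|---|---|---|
| Selective, suppressed gland, s = 0.25 to 0.99 | 0.25 to 0.99 | 5 to 40 |
| Missed vein, pure IVC blood | 1.00 | 1.0 |
| Missed vein, 2% to 10% adrenal blood from a suppressed gland (s = 0.25, k = 20) | 0.78 to 0.48 | 1.4 to 2.9 |
| Missed vein, 2% to 10% adrenal blood from a dominant gland (s = 4, k = 20) | 1.87 to 3.07 | 1.4 to 2.9 |

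For admixture fraction m and k = 20, the index is [(1 − m) + 20·m·s]/[(1 − m) + 20·m]. At m = 0.10 and s = 0.25 this is 1.4/2.9 = 0.48; at m = 0.10 and s = 4 it is 8.9/2.9 = 3.07. The cortisol ratio is (1 − m) + 20·m, which is 1.38 at 2% and 2.90 at 10%.

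**3. Effect of the maximum in the denominator.** A sample equal to a typical IVC draw scores 1/(1 + d): 1/1.05 = 0.95, 1/1.10 = 0.91, 1/1.20 = 0.83. A fixed cut-off is applied across patients, so a missed vein at 0.83 to 0.95 in one patient overlaps with a correctly sampled, mildly suppressed gland in another.

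**4. Reading.** Under marked suppression (index below 0.5) a good sample scores below a fully missed vein. Nearer 1 the two overlap, and admixture moves missed samples in either direction. No cut-off separates them. Over the same assumed ranges the cortisol ratio gives 5 to 40 against 1.0 to 2.9.

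**5. Patients whom the technical-failure exclusion concerns.** In section 33, surgery is expected in every cell with a unilateral result on either test: C+D+G+H+I+J+K+L+M+O+P+Q = 1+10+1+9+0.5+3.5+1+29+4×0.25 = 56%. Unsuccessful AVS among these is C+D = 11%, so 11/56 = 19.6%. That is about 14 of 70 operated patients (Protocol section 23) or 18 of 90 (synopsis). This is the planned size of the excluded group, not a count of misclassified patients.

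**The case against.** The strongest reply is that nothing depends on the index. It stands in a descriptive list under baseline characteristics. No text makes it decide technical failure, the inconclusive AVS category, the treatment decision or the primary analysis. In 2.2.2 the AVS result is the grouping variable and the index is one of the measures summarised within groups, so the grouping is not shown to come from it. Protocol 11.0 reads lateralisation from a four-fold A/C difference at the monthly multidisciplinary meeting, and Protocol 24.3 has an endpoints committee assess AVS without knowledge of surgical outcome. Adrenal-vein and IVC cortisol are both summarised, so the step-up can still be derived. All of this stands, and it limits the consequence.

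A reader might infer that the definition reverses the one planned sensitivity analysis, failing good studies and passing missed veins. The documents do not support that. The index is not tied to 2.3.6, and reversal would need a threshold lying between the two scores; the SAP states none. Any threshold above 1.0 would also fail a missed vein of pure IVC blood.

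A reader might also infer that a suppressed, selective sample always scores below a missed vein. Steps 2 and 3 show that this is secure only for marked suppression. Nor does Protocol 11.0's own lateralisation rule require suppression; that condition is in 4.2.

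Finally, neither document says outright that cannulation is judged from cortisol. Protocol 6.2 also lists metanephrines among the AVS measurements, but SAP 2.2.2 does not summarise them and neither document gives them this role.

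None of this rescues the definition, which is wrong even as a line in a summary table.

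**Conclusion.** The concern holds as a mislabelled measure. As written, the SAP would report a Selectivity Index that contains no information on the cortisol step-up, equals the suppression ratio of 2.3.2 on the non-dominant side, and does not discriminate between selective and missed samples. Cancellation of the step-up is exact and needs no assumption. The comparison with missed veins assumes that they give IVC-like blood, pure or with a small adrenal admixture; the step-up and IVC-spread ranges are illustrative.

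No corrupted primary result is shown. The risk to the exclusion in 2.3.6, a planned 20% of operated patients, arises only if this index were used there. The absence of any definition of technical failure leaves that possibility open. Severity is minor to moderate.

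**What to change.** - In SAP 2.2.2, define the Selectivity Index on each side as adrenal-vein cortisol divided by mean low-IVC cortisol. Both are already in the list.
- Report the A/C-to-IVC ratio under the contralateral-suppression name of SAP 2.3.2, and state which IVC summary (mean or maximum) forms its denominator in both places.
- In SAP 2.3.6, state that technical failure is decided from the cortisol index or from the blinded AVS classification, and not from the A/C ratio. If the cortisol index is used, the sponsor should state its cut-off before analysis, so that the exclusion cannot be chosen after results are seen. The documents give no cut-off and none is proposed here.

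The cost is one SAP line per side, a change of label, and a sentence in 2.3.6. No new data are needed.
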